### Safety Review

Safety data will be presented as line lists of SAEs with descriptions and relatedness to study drug as well as tallies of grade 3 and 4 AEs by treatment arm. An excess of SAEs in one arm may lead the DSMB to recommend suspending the study, to request additional data or to request another safety analysis at a specified interval.

### Efficacy Review

The study examines treatment efficacy over the course of a year. As longer term data will not be available at the interim review, the interim review will focus on initial treatment administration and 28-day clinical treatment outcomes. Less than or equal to 75% adequate clinical response at day 28 will lead to a discussion in the DSMB about suspension of that arm of the trial, although this circumstance will not constitute a formal halting rule. The efficacy of all study arms is likely to be very high as all treatment arms contain full dose chloroquine whose short-term efficacy alone is expected to exceed 95%.

## Final Analysis Plan

The final analysis of the primary objective will be a comparison of incidence rates of malaria treatment episodes per year of follow-up (not including the first infection occurring at enrollment) in each arm of the study. The rates and 95% confidence intervals will be calculated using Poisson distribution. Reported antimalarial drug use without documented positive malaria smear will not count as a malaria treatment episode. Malaria episodes treated with non-study medicines at Queen Elizabeth Central Hospital with verified positive malaria smears will be counted as malaria treatment episodes, and any such treatments will be compared among groups to rule out bias due to different rates of non-study treatment. Withdrawal of participation is described above and includes participants who miss ≥ 2 consecutive routine follow-up visits. For the primary study endpoint, follow-up time for participants while they are enrolled in the study will be included in the analysis. For participants who were withdrawn after missing > 2 consecutive follow-up visits, time after the last visit will be censored from incidence analysis.

Drug efficacy for the first and subsequent episodes of malaria will be compared using Kaplan-Meier 28-day survival estimated and compared using Cox proportional hazards regression. Per-protocol analysis will be used to compare treatment efficacy, with data excluded from treatment episodes for which treatment outcome cannot be determined. Survival analysis will also be used to assess time to first resistant infection in each arm. Categorical data including episodes of liver, kidney or neurological toxicity and presence of anemia will be compared using 2 analysis. Logistic regression will be used to adjust for covariates.

Survival analysis will be used to assess the role of travel outside of Blantyre and bed net use on the risk for malarial and time to first malaria episode. This analysis will be conducted both with and without the inclusion of treatment arm as a covariate in the analysis.

Data will be entered in to the database on the computers at the field site. On a daily basis, the data will be transferred via the internet to the EMMES corporation web-based system.

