## Sample Size Considerations

In a previous longitudinal study of malaria in this population, we found that the mean annual incidence of malaria was approximately 2.5 episodes per year (59) with a standard deviation of approximately 2. Chloroquine is presently highly effective in treating malaria and has a prolonged prophylactic effect, so we have estimated a mean rate of 1.5 malaria episodes per year with chloroquine alone. We derived the sample size required to detect a decrease in the mean to 1.0 episodes per year assuming a Poisson distribution and using a 2 sided test with alpha= .05/3=.0166. The test size was adjusted to accommodate the 3 treatment versus control comparisons. With the above requirements and for a 2 treatment contrast, 120 subjects with complete observation are required per treatment arm to have 90% power (PASS 2005). To account for migration and other causes of attrition, we will enroll an additional 33% (40 subjects) in each regimen. We will accrue 160 per arm for a total of 640 subjects.

Because of the currently estimated efficacy of chloroquine alone in Malawi (in excess of 95%), we are unlikely to determine differences in initial administration (day 28) efficacy between the treatment arms. Power is limited as all arms should have very few early failures. Rates of anemia (<8 mg/dl) at the end of one year should be available in ~120 subjects per arm. The 95% CI half-width for the difference in anemia rates, calculating the variance with a rate of .2, is approximately .10. Thus, the selected sample size should be informative about larger treatment arm differences in anemia rates.

To determine the population pharmacokinetic curve for chloroquine, we have designed a randomized unbalanced study. All participants will have chloroquine levels determined prior to drug administration, at day 14 and at one additional randomly assigned time point. The assignment will be weighted to increase measurement on day two. Planned Interim Analyses

The DSMB will decide when it would like to conduct the interim analysis. The data to be reviewed at this meeting will include safety and efficacy data.

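### The primary rates and 95% intervals are tied to the Poisson distribution, although the protocol's own planning SD points to extra-Poisson variation between children

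*Protocol*

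**What the plan says.** The Final Analysis Plan (11.3) makes the primary analysis a comparison of episode rates between arms. The enrolment episode is left out and time under follow-up is the denominator. On method it says: "The rates and 95% confidence intervals will be calculated using Poisson distribution". For this endpoint it gives no scale factor, robust variance or other allowance for variation between children. It names no between-arm test and does not restate a test level.

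Sample Size Considerations (11.2) describes the incidence in an earlier longitudinal study in this population as "approximately 2.5 episodes per year (59) with a standard deviation of approximately 2". For the present trial it says "we have estimated a mean rate of 1.5 malaria episodes per year with chloroquine alone", and the target is a fall to 1.0. The sample size was derived "assuming a Poisson distribution and using a 2 sided test with alpha= .05/3=.0166". The reason for the level is also given: "The test size was adjusted to accommodate the 3 treatment versus control comparisons". The result is 120 children per arm with complete observation for 90% power, raised to 160 for attrition.

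**The concern.** A Poisson count has variance equal to its mean, so a mean of 2.5 goes with an SD of √2.5 = 1.58, not 2. The larger figure suggests that some children have more episodes than others beyond chance. The protocol itself expects unequal risk: it enrols from 6 months to 5 years of age, describes a seasonal peak, plans a search for spatial clusters, and studies travel and bed net use as risk factors.

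If risk differs between children, Poisson standard errors are too small and the intervals on the primary endpoint too narrow. If the arm comparisons use the same variance, a combination could be declared better than chloroquine more often than the .05/3 level allows.

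**Working it through.** **Inputs from 11.2.** Earlier mean about 2.5 and SD about 2; planned rates 1.5 (chloroquine) and 1.0; two-sided .05/3 per comparison, so z = 2.394; 90% power, so z = 1.282; 120 completers per arm; three comparisons sharing one control arm.

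**1. The plan's own figure.** The Wald sample size for Poisson regression on a binary covariate, with variance equal to the mean, is

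N = (2.394·√4 + 1.282·√5)² / (1.5·(ln 1.5)²) = 237.5 in total, or 118.8 per arm.

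That is close to the stated 120. Other common two-sided Poisson formulas give 134 to 137. The stated figure therefore contains no allowance for dispersion above 1.

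**2. Dispersion φ (variance/mean) implied by the cited figures.**
- At the earlier mean: 2²/2.5 = 1.6.
- Negative binomial: (4 − 2.5)/2.5² = 0.24, so at a mean of 1.5, φ = 1 + 0.24 × 1.5 = 1.36.
- Both values are carried forward, since the documents do not say which relation holds.

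**3. Interval coverage.** True coverage of a nominal 95% Poisson interval is 2Φ(1.96/√φ) − 1. A valid interval is √φ times as wide.

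**4. Error rates, if the test also uses Poisson variance at .05/3.** Per comparison: 2(1 − Φ(2.394/√φ)). Over three comparisons: trivariate normal with correlation 0.5 from the shared control.

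| φ | Coverage of 95% interval | Valid width relative to Poisson | Error per comparison | Error over three |
|---|---|---|---|---|
| 1 | 95.0% | 1.00 | 1.7% | 4.5% |
| 1.36 | 90.7% | 1.17 | 4.0% | 10.2% |
| 1.6 | 87.9% | 1.26 | 5.8% | 14.5% |

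Simulated negative binomial counts (200,000 four-arm trials at 1.5 per year, 120 or 160 per arm, naive Poisson z-test) give 10.1–10.2% and 14.3–14.4% in the last column.

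**5. Sensitivity to rounding.** Taking means of 2.25 to 2.75 and SDs of 1.75 to 2.25, with φ derived either way, the three-comparison error runs from about 5% (φ = 1.06) to about 26% (φ = 2.25).

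**The case against.** **No test is fixed.** The quoted sentence covers rates and intervals, and a Poisson regression with scaled or robust errors would not plainly contradict it. The between-arm model is commonly left to a SAP, which was not available here. This stands. A reader might infer that the protocol commits itself to a 10–14% false-positive rate; the text does not support that without the added assumption of a naive Poisson test. The interval problem needs no such assumption, because the intervals are stated.

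**The SD may not be overdispersion.** 11.2 does not say whether the SD is of full-year counts or of annualised rates with unequal follow-up. Suppose, as an assumption, that 80% of children were followed for a year and 20% for three months. Pure Poisson counts at 2.5 per year would then give annualised rates with variance 2.5 × (0.8/1 + 0.2/0.25) = 4, an SD of exactly 2. A person-time analysis removes that kind of variation. The follow-up in the earlier study is not in the documents, so this cannot be settled.

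**Carry-over is assumed.** The earlier study used other drugs. Here every arm contains chloroquine, with a long prophylactic effect, and recurrences within 14 days count as failures and not as new episodes. Event-free time after treatment lowers count variance: simulating the 0.24 heterogeneity at 1.5 per year gives φ of about 1.17 with a 14-day gap and 1.01 with a 28-day gap. At 1.17, coverage is 93.0% and the per-comparison error 2.7%. This also stands, except that the earlier SD may already contain part of the effect.

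**95% intervals beside tests at .05/3.** A reader might see a contradiction between 11.3 and 11.2. There is none: descriptive 95% intervals can accompany tests at a stricter level, and nothing says that the 95% intervals decide superiority. If they did, the three-comparison error would be about 12.5% even with true Poisson counts, which is reason enough to state the level.

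**Conclusion.** The point holds as a stated method that conflicts with the only dispersion figure in the protocol. At the cited mean and SD, and if that variation carries over, the nominal 95% intervals cover about 91% (φ = 1.36) or 88% (φ = 1.6) and are 14% or 21% too narrow (1 − 1/√φ).

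The error rate over the three comparisons of about 10% or 14%, against under 5%, rests on one further condition: that the unnamed test uses Poisson variance at .05/3. It is the value at the stated inputs and not a bound. Rounding alone gives about 5% to 26%, and unequal follow-up in the earlier study or post-treatment prophylaxis could make the true dispersion smaller. The SD is a warning sign and does not prove overdispersion in this trial. A robust method is preferable because it remains valid in either case.

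**What to change.** Replace the Poisson sentence in 11.3 with a dispersion-robust analysis on person-time, for example:

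> Episode counts will be analysed by negative binomial regression (or Poisson regression with robust standard errors), with log time at risk as offset and arm as factor. Per-arm rates and intervals come from this model. The three rate ratios versus chloroquine are each tested at two-sided .05/3, and any interval used to judge superiority is at the matching 98.3% level.

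One of the two models should be chosen before the data are seen. This fix needs no age covariate.

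The cost is wording only, with no new data, visits or recruitment. Intervals become somewhat wider where dispersion is present and hardly change where it is not. Power at 120 per arm should then be read realistically. With the unpooled formula Φ(0.5/√((v₁+v₀)/120) − 2.394), it is 86% for Poisson variances (1.5 + 1.0). It falls to 74% with negative binomial variances (1.5 × 1.36 + 1.0 × 1.24 = 3.28) and 63% with φ = 1.6 in both arms (2.4 + 1.6 = 4.0). That loss comes from the dispersion, if it is real, and not from the change of method.

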# Background Information and Scientific Rationale

## Background Information

In 1993, Malawi was the first sub-Saharan African country to discontinue the routine use of chloroquine and to elevate the antifolate combination sulfadoxine-pyrimethamine (SP) to the antimalarial of first choice nationwide. The decision was based on chloroquine's increasing failure to produce adequate clinical and hematological recovery (1). Since 1993 SP has been the only available treatment for uncomplicated malaria in all government health facilities, and is dispensed without prescription. Although chloroquine has remained available by prescription and through unauthorized private sources, a national information campaign was largely successful in convincing health practitioners and the public to accept SP as the treatment of choice for children with malaria.

It has been speculated that years of reliance on antimalarials other than chloroquine might lead to the reemergence of chloroquine-sensitive *P. falciparum* and permit the reintroduction of this safe and affordable drug. We retrospectively measured the prevalence of the *pfcrt* 76T molecular marker for chloroquine-resistant *P. falciparum* malaria in Blantyre, Malawi. From 1992 to 2000, we documented a gradual decrease in prevalence of the mutation associated with chloroquine resistance (2) and neither we nor other investigators have found any parasites with the mutation since 2001 ([name], personal communication and [name], personal communication).

We have demonstrated the clinical efficacy of chloroquine, as well. In preparation for the present study, we conducted a trial to assess the efficacy of chloroquine in treating children with uncomplicated malaria at the Blantyre Malaria Project Research Clinic at the Ndirande Health Centre from May through December, 2005. Two hundred ten children with uncomplicated malaria were randomly assigned to receive either SP, the standard therapy in Malawi, or chloroquine. Among 105 children randomized to receive chloroquine monotherapy, only one experienced treatment failure. The results are shown in Table 1. Based on these results, we have determined that chloroquine is safe to use to treat malaria in this population.

|  | Chloroquine | SP |
| --- | --- | --- |
| Adequate clinical and parasitologic response (% per-protocol) | 79 (99) | 16 (18) |
| Early treatment failure (% per-protocol) | 1 (1) | 21 (24) |

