## Study Outcome Measures

### Primary Outcome Measures

- The number of clinical malaria episodes per year of follow-up.

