### Secondary Outcome Measures

1. To assess the antimalarial drug efficacy at first administration, by treatment arm.

- Rate of adequate clinical and parasitologic response 28 days after initial malaria

The 28 day outcomes represent the standard assessment of antimalarial efficacy and provide important information about the short term benefits of the drug. Since we will assess the ability of combination therapy to protect against the emergence of resistance, we are most interested in clinically apparent, in vivo drug efficacy.

- The incidence of new infections and recrudescent infections after initial treatment in each treatment arm

Parasites that emerge after treatment may be classified as new infections (arising from a new exposure) or recrudescent infections (arising from the original infection). Drugs that have poor efficacy but long half-lives may protect against new infections, but fail to cure the original infection completely. In contrast, shorter acting but highly effective medications may treat the initial infection successfully, but leave the individual susceptible to new infections in areas of high transmission. Distinguishing these two mechanisms will help to elucidate the complex interaction between the drugs and the parasite population.

1. To assess the antimalarial drug efficacy during subsequent episodes of malaria, by treatment arm.

- Rate of adequate clinical and parasitologic response 28 days after subsequent new episodes of malaria
- The incidence of new infections and recrudescent infections after subsequent new episodes of malaria

The same outcomes measured after the first administration will be monitored for subsequent administrations. This ability to detect efficacy after repeated use is a strength of the longitudinal study design.

- Incidence of severe malaria

Although children who present with severe malaria will be excluded from enrollment in the study, subsequent episodes of severe disease in study participants will be assessed as study endpoints. We would expect severe malaria to be rare in this population when children are treated promptly and effectively. A significant difference in the rate of severe disease, if detected, would be an important finding.

1. To measure the prevalence of chloroquine resistant parasites during the trial, by treatment arm.

- The prevalence of parasites with the mutation *pfcrt* 76T on Day 0 of each episode of malaria

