## Follow-up

Follow-up visits may be one of four types: day of new malaria episode diagnosis, drug efficacy follow-up, routine visit, unscheduled visit.

On the initial day of a new diagnosis, a venipuncture will be performed to obtain the following studies: filter paper sample for molecular analysis, CBC, ALT, creatinine, chloroquine level and specimen for cryopreservation of parasites. The total volume will be approximately 3.5-5 mL.

Drug efficacy follow-up occurs after the initial and all subsequent administrations of the study drug to treat symptomatic malaria. Visits will occur on days 1, 2, 3, 7, 14, 21, 28. Hemoglobin, malaria smears and filter papers will be obtained on each of those days and a physical examination will be completed. Specimens from a finger prick will be obtained on two occasions after day 0: on day 14 and an additional day assigned randomly at enrollment. Chloroquine level, CBC, ALT and creatinine will be measured routinely on day 14, after acute changes associated with malaria should have resolved If the participant misses the visit corresponding to the day a chloroquine level and/or CBC, ALT and creatinine arescheduled to be collected, the study team will endeavor to collect this specimen as the next visit. Drug administration will occur on days 1 (2nd dose) and 2 (3rd dose).If treatment failure occurs after day 3 and the parasite density is >10,000/mm3, blood will be collected to measure the chloroquine level and for cryopreservation of malaria parasites for further in vitro susceptibility testing. A neurologic exam will occur on day 28.

Routine visits occur every four weeks. Malaria smear and filter paper will be obtained. The malaria smear will be read at that time only if there are complaints of an illness or the clinician suspects malaria. The encounter will include an interval history, questions about off-study drug use, recent travel, bed net use and a physical examination. At routine visits 4, 8 and 13, CBC, ALT and creatinine will be obtained for safety monitoring surveillance. All blood specimens will be collected from a finger prick except for the specimens for cryopreservation which require 3-5 ml. On all other days, the amount of blood drawn from the finger prick will range from 0.05 ml (malaria smear, hemoglobin, filter paper) to approximately 0.5 ml (malaria smear, hemoglobin, filter paper, CBC, ALT, creatinine and chloroquine level).

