## Clinical Evaluations

*History-comprehensive*

- The medications administered to the child in the past week
- Any underlying medical conditions
- Allergies
- Recent travel history and bed net use

*History-possible adverse drug reactions and interval*

A standardized checklist in the case report form includes symptoms of malaria, as well as most common adverse effects of the drugs being administered.

*Questioning about antimalarial use*

The parent/guardian will be asked if any drugs have been administered to the child in the interval since the last visit. The clinician will then specifically ask about the commonly administered antimalarial drugs.

*Physical examination*

The physical examination includes vital signs (temperature, heart rate, respiratory rate), weight, height and a complete physical examination that focuses on: signs of malaria, signs of non-malaria sources of fever and adverse reactions to the medications.

*Neurological examination*

A basic age-appropriate neurological examination will be conducted at the end of every episode of malaria treatment if the participant is not ill (day 28) and also at visit number 4, 8 and 13. See appendix IV.

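### Comparing the hospital-treated episodes that are already counted cannot rule out bias from non-study treatment; unsmeared antimalarial use needs a by-arm comparison too

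*Protocol*

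**What the plan says.** The primary outcome (Protocol 3.2.1) is "The number of clinical malaria episodes per year of follow-up". Section 11.3 (Final Analysis Plan) adds three linked statements about treatment outside the study:

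- Not counted: "Reported antimalarial drug use without documented positive malaria smear will not count as a malaria treatment episode".
- Counted: "Malaria episodes treated with non-study medicines at Queen Elizabeth Central Hospital with verified positive malaria smears will be counted as malaria treatment episodes".
- Check on bias, in the same sentence as the counting rule: "any such treatments will be compared among groups to rule out bias due to different rates of non-study treatment".

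The protocol also collects drug use from outside the study. For routine visits, section 7.3 says: "The encounter will include an interval history, questions about off-study drug use, recent travel, bed net use and a physical examination". Section 8.1 adds: "The clinician will then specifically ask about the commonly administered antimalarial drugs". Appendix I lists questions on medication use at routine visits and on antimalarial use at each drug-efficacy visit.

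**The concern.** The treatments to be compared are, by their grammatical antecedent, the smear-verified hospital treatments. These already contribute to the episode count. The other class, antimalarials taken without a smear, is removed from the count in the preceding sentence and is given no comparison by arm. An episode treated that way can drop out of the numerator, and the drug may suppress later parasitaemia.

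The protocol's own text makes this class plausible. Under Background Information, SP "is dispensed without prescription", and chloroquine is said to remain obtainable by prescription and from unauthorised private sources. The trial is open label (5.4.2), so families know the assigned regimen and could seek treatment elsewhere at rates that differ by arm.

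The hospital treatments may also be few. Section 3.2.2 says of severe malaria: "We would expect severe malaria to be rare in this population when children are treated promptly and effectively". A similar rate across arms in a handful of events would then carry a claim about the validity of the primary comparison that it cannot support.

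**Working it through.** **1. Scope of the check, from section 11.3.**

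| Non-study treatment | In the primary count? | In the stated comparison (plain reading)? |
|---|---|---|
| Referral hospital, smear verified | Yes | Yes |
| Reported antimalarial use, no documented positive smear | No | No |

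The class that can cause under-counting is the class that is not compared.

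**2. Inputs.** From section 11.2: 1.5 versus 1.0 episodes per child-year, Poisson, two-sided alpha 0.05/3 (critical value 2.394), 120 children per arm observed for a year. The protocol gives no rate of off-study treatment and no figure for the bias check, so all off-study rates below are assumptions.

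**3. The plan's own figure.** The standard error of the rate difference is √((1.5 + 1.0)/120) = 0.1443, and 0.5/0.1443 = 3.464. Power = Φ(3.464 − 2.394) = Φ(1.070) = 86%. The plan states 90%. That gap is a separate matter; 86% is only the starting point for step 6.

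**4. How often a doubling of hospital treatments would be missed.** The protocol names no test. For illustration I take a two-sided 5% level, 120 child-years per arm, and two tests of equal Poisson rates: z = (x − y)/√(x + y), and the exact conditional binomial test. Expected events are rate × 120.

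| Assumed rates per child-year | Expected events | Missed, z test | Missed, exact test |
|---|---|---|---|
| 0.02 vs 0.04 | 2.4 vs 4.8 | 87% | 94% |
| 0.05 vs 0.10 | 6 vs 12 | 70% | 78% |
| 0.10 vs 0.20 | 12 vs 24 | 48% | 55% |

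**5. The same point without a test.** Suppose the two arms show identical counts e. The approximate 95% interval for the rate ratio is exp(±1.96 × √(2/e)).

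- e = 2.4 (the expected count): √(2/2.4) = 0.913, interval 0.17 to 6.0.
- e = 6: √(2/6) = 0.577, interval 0.32 to 3.1.
- e = 12: √(2/12) = 0.408, interval 0.45 to 2.2.

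Even a perfect match leaves a doubling in either direction inside the interval.

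**6. What uncounted episodes could do to the primary test.** Suppose unsmeared treatment removes a net 0.15 episodes per child-year (10% of 1.5) from one arm only.

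- Removed from chloroquine alone, true rates 1.5 and 1.0: observed 1.35 and 1.0. SE = √(2.35/120) = 0.1399; 0.35/0.1399 = 2.501; power = Φ(2.501 − 2.394) = 54%, down from 86%.
- Removed from a combination arm, both true rates 1.5: observed 1.5 and 1.35. SE = √(2.85/120) = 0.1541; 0.15/0.1541 = 0.973; rejection probability = Φ(0.973 − 2.394) + Φ(−0.973 − 2.394) = 7.8%, up from 1.7%.

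Neither shift would appear in a comparison of the counted hospital treatments.

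**The case against.** Five points can be made for the plan.

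- **The protocol says only that treatments will be compared.** A reader might infer that a non-significant test will be reported as proof of no bias. The text names no test, p-value or decision rule, so that is not supported. The method of comparison can also properly be left to a statistical analysis plan. What stands is narrower: the protocol itself fixes both the scope of the comparison and the claim it is to support, and step 5 needs no test.
- **The purpose clause speaks of non-study treatment in general.** A loose reading would take in all off-study use. If that is meant, the sentence needs rewording to say so, and ruling bias out is still too strong.
- **Counted hospital treatments are not harmless.** A reader might infer that they cannot bias the result because they are in the count. That is wrong: a non-study drug replaces the assigned regimen and its post-treatment protection, so unequal use can change later incidence. Comparing them has value.
- **The design limits off-study use.** A study clinician is available daily, care is provided at the study clinic, visits are four-weekly and missed visits are traced. These features should lower the rate, but they do not show that it is equal across arms.
- **Unsmeared treatment is often not malaria.** Counting every such course as an episode conflicts with the smear-based case definition. That is right for the primary endpoint, so such a count can serve only as a bounding analysis.

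**Conclusion.** The point holds as a correction to a stated validity claim about the primary endpoint. On the plain reading of section 11.3, the check covers only events already counted, gives no by-arm view of the use that is excluded, and cannot rule out bias. At assumed rates of 0.02 to 0.10 hospital treatments per child-year in one arm and 120 child-years per arm, a doubling in the other arm would be missed about half to nine-tenths of the time (48% to 94% across the two tests).

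A reader might go further and conclude that the primary comparison is biased, or that power will fall to 54% or the error rate rise to 7.8%. The documents do not support that. They give no off-study treatment rate, no evidence of a difference between arms and no direction. The step 6 figures also assume a net loss of 0.15 counted episodes per child-year confined to one arm. They show what the stated check could fail to reveal, not what will happen.

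**What to change.** In section 11.3:

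1. Replace the claim of ruling out bias with *to assess potential bias*. Replace the reference back to the hospital treatments with *all reported non-study antimalarial use, with or without a smear and from any source*. Report it by arm as rates, and as rate ratios versus chloroquine monotherapy with confidence intervals.
2. Keep the smear-based primary endpoint and pre-specify two sensitivity analyses. One counts each reported unsmeared antimalarial course as an episode, labelled as a bounding case. The other removes a period after each non-study course from follow-up time, with its length fixed in advance.
3. Base any statement about bias on whether the primary rate ratios change across these analyses.

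The cost is a change of wording and a little extra analysis on data the visits already collect. The drawback is that the bounding analysis will include some illnesses that were not malaria, so it should not be read as a second estimate of the treatment effect.
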